# Dual bronchodilators in Bronchiectasis study (DIBS): protocol for a pragmatic, multicentre, placebo-controlled, three-arm, double-blinded, randomised controlled trial studying bronchodilators in preventing exacerbations of bronchiectasis

**DOI:** 10.1136/bmjopen-2023-071906

**Published:** 2023-08-10

**Keywords:** RESPIRATORY MEDICINE (see Thoracic Medicine), Adult thoracic medicine, Clinical trials

## Abstract

**Introduction:**

Bronchiectasis is a long-term lung condition, with dilated bronchi, chronic inflammation, chronic infection and acute exacerbations. Recurrent exacerbations are associated with poorer clinical outcomes such as increased severity of lung disease, further exacerbations, hospitalisations, reduced quality of life and increased risk of death. Despite an increasing prevalence of bronchiectasis, there is a critical lack of high-quality studies into the disease and no treatments specifically approved for its treatment. This trial aims to establish whether inhaled dual bronchodilators (long acting beta agonist (LABA) and long acting muscarinic antagonist (LAMA)) taken as either a stand-alone therapy or in combination with inhaled corticosteroid (ICS) reduce the number of exacerbations of bronchiectasis requiring treatment with antibiotics during a 12 month treatment period.

**Methods:**

This is a multicentre, pragmatic, double-blind, randomised controlled trial, incorporating an internal pilot and embedded economic evaluation. 600 adult patients (≥18 years) with CT confirmed bronchiectasis will be recruited and randomised to either inhaled dual therapy (LABA+LAMA), triple therapy (LABA+LAMA+ICS) or matched placebo, in a 2:2:1 ratio (respectively). The primary outcome is the number of protocol defined exacerbations requiring treatment with antibiotics during the 12 month treatment period.

**Ethics and dissemination:**

Favourable ethical opinion was received from the North East—Newcastle and North Tyneside 2 Research Ethics Committee (reference: 21/NE/0020). Results will be disseminated in peer-reviewed publications, at national and international conferences, in the NIHR *Health Technology Assessments* journal and to participants and the public (using lay language).

**Trial registration number:**

ISRCTN15988757.

Strengths and limitations of this studyLarge randomised controlled trial to address unmet clinical need and critical lack of research into bronchiectasis treatments.Pragmatic trial design conducted over multiple sites in the UK.Challenge of delivering a large multicentre trial in the respiratory disease area in the peri-COVID-19 era.Challenge of a static trial design with changing biology of bronchiectasis following shielding behaviours during the COVID-19 pandemic.

## Introduction

Bronchiectasis is a chronic lung condition, characterised by dilated bronchi, leading to symptoms of breathlessness and chronic productive cough, with intermittent infective exacerbations. Bronchiectasis has various potential aetiologies including immune-deficiency syndromes, allergic bronchopulmonary aspergillosis, chronic obstructive pulmonary disease (COPD), ciliary dysfunction and postinfectious, yet studies have found that between a quarter and half of cases are idiopathic.^1 2^ Patients often have recurrent, costly hospital admissions, a poorer quality of life^3 4^ and clinically significant fatigue.^5 6^

Current estimates suggest a prevalence of 100 000 adult patients with the condition in the UK. Importantly, studies demonstrate that up to 50% of patients with COPD have coexistent bronchiectasis.^7^ With approximately 1 000 000 patients with COPD in the UK,^8^ there is potential for a significant increase of case-finding of COPD-associated bronchiectasis over the coming years.

Bronchiectasis mortality rates are approximately 50% higher than that of uncomplicated COPD (calculated at 3% per annum) and have been reported to be increasing.^9^ Prognosis varies, with a prior study of 91 patients^10^ finding that the primary cause of death was usually respiratory, with survival rates of 91% at 4 years and 68.3% at 12.3 years. The same study found factors such as chronic infection with *Pseudomonas aeruginosa* increase mortality.

Multicentre data suggest that the Bronchiectasis Severity Index (BSI), a multicomponent clinical scoring system, is useful in predicting both mortality and morbidity (hospitalisation). This score was validated in 1300 patients across Europe.^11^

Infective exacerbations lead to significant morbidity. Within the UK national audit data patient group, average exacerbation rate is approximately 3 per year (nearly twice the rate of COPD) with an attendant risk of hospitalisation. This is consistent with published American data on the increasing burden of bronchiectasis^12^ and in the UK.^13^ Previously published UK data also emphasise the burden of bronchiectasis, uncertainties in aetiology and lack of evidence for the treatments that are often used.^14^ Hence, improved interventions in bronchiectasis are urgently required.

There is no cure for bronchiectasis. Current modalities of treatment include oral, inhaled or intravenous antibiotics given regularly with additional courses administered for exacerbations. Mucolytics and regular physiotherapy are used to aid sputum clearance and there are additional guidelines for investigation, diagnosis and management of bronchiectasis produced by the British Thoracic Society (BTS).^15^

National audits in the UK suggest up to 80% of patients with bronchiectasis are on inhaled therapy despite limited evidence.^15^ Prior studies of inhaled corticosteroids (ICS) in bronchiectasis have shown no clear benefit^15^ and are therefore not recommended in prevailing bronchiectasis guidelines. ICS, however, have been shown to have benefits in asthma^16^ and in COPD.^17^ More recent data emerging from COPD suggests that ICS reduce COPD exacerbation rates but increases pneumonia rates, a side effect that may be very pertinent in bronchiectasis. International guidelines for COPD now suggest a selective application of ICS and that not all patients with COPD benefit from ICS therapy^17^

The role of triple therapy (ICS/LABA/LAMA) and dual bronchodilation (LABA/LAMA) therapy is unclear in bronchiectasis with no robust randomised placebo-controlled data available. Given the likely higher bacterial and inflammatory load in bronchiectasis airways, these therapies need to be specifically studied within this population

## Methods and analysis

Trial methods and analysis are reported as per Standard Protocol Items: Recommendations for Interventional Trials reporting guidelines.^18^

### Trial design

Dual bronchodilators in bronchiectasis study (DIBS) is a pragmatic, multicentre, placebo-controlled, three-arm, double-blinded, randomised controlled trial, incorporating an internal pilot. The trial aim is to recruit a total of 600 adult patients with bronchiectasis from up to 25 secondary care National Health Service (NHS) sites. The trial is Sponsored by The Newcastle upon Tyne Hospitals NHS Foundation Trust ([contact]).

The internal pilot involves approximately 15 secondary care NHS sites recruiting for a 12 month recruitment period (following activation of the first site to recruitment). Site activation of the NHS sites will be as soon as possible with a staggered approach. The recruitment aim is to recruit 98–125 participants equating to an average recruitment between 1.25 and 1.6 participants recruited per site per month. At the end of the internal pilot, a review will be made by the Trial Management Group (TMG), the Trial Steering Committee (TSC), the Independent Data Monitoring and Ethics Committee (IDMEC) and a consultation with the funder against the following progression criteria to proceed from the internal pilot to the main trial recruitment:

Average recruitment ≥1.6 participants/month/site activated—continue to main trial and open additional sites (up to 25 sites total)Average recruitment ≥1.25 participants/month/site activated—continue to main trial and open additional sites (up to 25 sites total) plus provide an improvement plan after identifying barriers to recruitment through discussion with sites, TMG, TSC and IDMEC as required.Average recruitment <1.25 participants/month/site activated—seek further guidance from funder

The TSC and IDMEC are composed of independent experts in the field (clinicians and statisticians) and patient a public representatives. Each committees’ roles are defined in their charters.

The main trial phase will follow on from the pilot without a break in recruitment. The main phase of the trial will involve an additional 10 secondary care NHS sites bringing the total number of sites recruiting to the trial to 25 sites. The recruitment target for each site remains 1–2 patients per month throughout the main phase of recruitment which will last for 14 months. The last patient’s last visit will be 12 months after the last participant has been recruited.

### Patient eligibility—inclusion and exclusion criteria

Patients are eligible for the trial if all of the following inclusion criteria apply:

Adult patients with CT scan confirmed bronchiectasis and bronchiectasis is the predominant primary respiratory disease in the view of the investigator (CT images/CT reports must be available to complete radiological scoring for BSI).History of two or more exacerbations in any 12 month period in the preceding 2 years requiring antibiotics and/or steroids.Evidence of airflow limitation with an forced expiratory volume in 1 s/forced vital capacity (FEV_1_/FVC) ratio less than 0.7 and/or daily mucus expectoration.Have either (1) less than 20 pack year history of smoking or (2) greater than 20 pack year history of smoking with FEV_1_ >79% predicted (to exclude COPD).For patients taking ICS, LAMA or LABA treatment prior to recruitment, willing to have these treatments changed or stopped.Stable bronchiectasis with no exacerbations for 4 weeks prior to baseline.Stable dose of oral steroid for 4 weeks prior to baseline (only applicable for patients taking oral steroid as part of standard care).

Patients are excluded from the trial if any of the following exclusion criteria apply:

Cystic fibrosis-related bronchiectasis.Where bronchiectasis is not the main disease or there are contraindications to ICS withdrawal.Predominant COPD or asthma.**Patients who have a historical diagnosis of asthma and/or COPD but where the investigator has sufficient evidence to refute these diagnoses can still be included.Indication to remain on ICS (eg, asthma, COPD, allergic bronchopulmonary aspergillosis and inflammatory bowel disease) or known intolerance to any of the trial drugs or their ingredients.Patients with galactose intolerance, total lactase deficiency or glucose-galactose malabsorption.Inability to perform spirometry or quality of life questionnaires.Patients who are:Pregnant.Breast feeding.Of childbearing potential with a positive urine pregnancy test prior to starting trial investigational medicinal product (IMP).Male or female of childbearing potential unwilling to use contraception throughout the trial (postmenopausal women must be amenorrhoeic for at least 12 months to be considered of non-childbearing potential).Anyone with cognitive impairment who may not be able to consent.Those who do not speak English or cannot comply with trial procedures.Any potential participant who the investigator believes will not be able to complete the trial visits and procedures.A history of allergy or hypersensitivity to any corticosteroid, anticholinergic/muscarinic receptor antagonist, β2-agonist, lactose/milk protein or magnesium stearate or a medical condition such as narrow-angle glaucoma, prostatic hypertrophy or bladder neck obstruction that, in the opinion of the investigator contraindicates trial participation.Use of acute antibiotics or systemic steroids within 4 weeks of baseline (except for antibiotics and/or stable doses of prednisone ≤5 mg used to treat non-respiratory conditions).Malignancy diagnosed within 5 years of the first trial medication administration where the investigator feels the trial may be affected by recurrence or progression of the malignancy (eg, patients with stable breast cancer, current prostate cancer or ‘expected curative’ cancer surgery) may not be excluded at the investigators discretion.Administration of an investigational agent within 30 days of first dose of trial medication.

### Objectives and outcomes

The primary objective for the trial is to compare the effects of inhaled dual bronchodilators either as a stand-alone dual therapy (LABA+LAMA) or in combination with ICS as a triple therapy (LABA+LAMA+ICS) to placebo on the number of protocol defined bronchiectasis exacerbations experienced per participant over the 12 month trial treatment period. The protocol definition of a bronchiectasis exacerbation is a continued worsening of one or more of symptoms including increased cough, sputum discolouration, excess sputum production, breathlessness and/or fatigue, that require treatment with antibiotic(s).

Additionally, there is a primary economic objective to compare the cost-effectiveness, measured in terms of incremental cost per quality-adjusted life-year (QALY) gained over the 12 month trial treatment period.

Secondary objectives include comparisons between the effects of dual therapy (LABA+LAMA), triple therapy (LABA+LAMA+ICS) and placebo on the number of bronchiectasis-related hospital admissions, the number of emergency hospital admissions, the time to the first exacerbation of bronchiectasis following randomisation, the number of adverse events (AEs) and cessation of treatment, quality of life, breathlessness and lung function, respiratory and cardiac mortality, economic costs and the incremental cost per QALY gained over the patient’s life course. Objectives and outcome measures are fully described in table 1.

**Table 1 T1:** Objectives and outcome measures

Objectives		Outcome measures
Primary	Compare effects of inhaled dual bronchodilators either as a stand-alone therapy (LABA/LAMA) or in combination with ICS (ICS/LABA/LAMA; triple therapy) therapy to placebo on the number of protocol defined bronchiectasis exacerbations (per participant)	Number of bronchiectasis exacerbations requiring treatment with antibiotics during 12 month treatment period as measured using participant reports and completed weekly exacerbation diary.
Primary economic	Compare cost-effectiveness measured in terms of incremental cost-per-QALY gained over the 12 month treatment period.	Incremental cost-per QALY at 12 months. Costs based on the cost of the interventions, use of health services via a Healthcare Utilisation Questionnaire administered at baseline, 1, 6 and 12 months postrandomisation and adverse events. Transport and time for participants to use healthcare appointments will be assessed via the Time and Travel Questionnaire administered at 12 months postrandomisation.
Secondary	To compare the effects of dual bronchodilators (LABA/LAMA) and triple (ICS/LABA/LAMA) therapy and placebo on:	
	Hospital admissions with a primary diagnosis of exacerbation of bronchiectasis	Number of hospital admissions for bronchiectasis exacerbations during 12 month treatment period as measured using participant reports and completed weekly exacerbation diary and verified where possible by hospital discharge summary/Hospital Episode Statistics (HES) data. Hospitalisation due to bronchiectasis exacerbation data collected up to 24 months after visit 1: screening/baseline will be used to extend modelling beyond 12 months as a sensitivity analysis.
	Time to first exacerbation of bronchiectasis	Time to first exacerbation of bronchiectasis as measured using participant reports/completed weekly exacerbation diary.
	Number of emergency hospital admissions	Number of emergency hospital admissions (all cause) as ascertained at 1, 6 and 12 months visits and where needed from primary care records.
	Adverse events/drug reactions and cessation of treatment	Number of adverse events/drug reactions and cessation of treatment as reported by participant to research team and at 1, 6 and 12 months visits.
	Disease related health status using the St Georges Respiratory questionnaire (SGRQ) and Quality of Life Bronchiectasis (QOL-B) questionnaire	SGRQ and QOL-B at baseline, 1, 6 and 12 months visits.
	Health-related quality of life using the EQ-5D-5L questionnaire	EQ-5D-5L at baseline, 1, 6 and 12 months visits.
	Breathlessness using Baseline and Transition Dyspnoea Indices (BDI and TDI)	BDI at baseline and TDI at 1, 6 and 12 months visits.
	Lung function using spirometry	Postbronchodilator lung function (LABA within 8 hours, short acting beta2 agonist within 2 hours) as measured by spirometry performed to AmericanThoracic Societyy/ European Respiratory Society (ATS/ERS) standards at baseline, 1, 6 and 12 month visits: Forced expiratory volume in 1 s (FEV_1_) Forced vital capacity (FVC)
	All-cause, respiratory and cardiac mortality	As ascertained from medical records or Office for National Statistics (ONS) records of trial participants (collected up to 24 months after visit 1: screening/baseline).
	Incremental cost per exacerbation avoided	Costs based on cost of the interventions (microcosted) and use of health services collected via a Healthcare Utilisation Questionnaire administered at baseline, 1, 6 and 12 months postrandomisation and adverse events collected via case report forms.
	Costs to the NHS and patients and lifetime cost-effectiveness based on extrapolation modelling	Data to populate the model will come from the trial and will be supplemented by HES and ONS data (collected up to 24 months after visit 1: screening/baseline) and by relevant literature and expert opinion and extrapolated over a patient lifetime.
	Rates of radiologically confirmed pneumonia, compared with participant’s normal baseline	Number of pneumonia events and total number of participants suffering pneumonia. This will be measured by asking the participants during follow-up visits.
Exploratory	To investigate the relationship between key outcomes (exacerbations and quality of life as measured by SGRQ and QOL-B) with baseline eosinophil (single level recorded at baseline), median eosinophil level (median of last three available recording when not on oral steroids) and baseline BSI	Eosinophil measurement at baseline and the median of the last three measurements available SGRQ and QOL-B as completed by participants at 1, 6 and 12 months follow-up visits BSI measured at baseline The number of protocol defined bronchiectasis exacerbations requiring treatment with antibiotics during 12 month treatment period as measured using participant reports/participant completed weekly exacerbation diary.

BSI, Bronchiectasis Severity Index; EQ-5D-5L, 5-level EuroQol5D index; ICS, inhaled corticosteroid; LABA, long acting beta agonist; LAMA, long acting muscarinic antagonist; NHS, National Health Service; QALY, quality-adjusted life-year.

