Adverse event reporting		X	X	X	X	X	X	
Review of primary care records						X		
Mortality data								X

EQ-5D-5L, 5-level EuroQol5D index; FEV_1_, forced expiratory volume in 1 s; FVC, forced vital capacity; GP, general practitioner.

Participants will be required to complete an Exacerbation Diary weekly throughout their 12 month participation in the trial. In this diary, participants will record whether or not they have experienced any exacerbations during the week and any steps or treatment taken for the exacerbation. This will be reviewed by a member of the research team at each trial visit and collected at the final 12 month follow-up.

Long term follow-up will be carried out 24 months after the screening/baseline visit for participants who reach this time point within the lifetime of the trial. Data collected at this time point are mortality data, the number of emergency hospital admissions and the number of emergency hospital admissions with exacerbations of bronchiectasis. Participants will not be contacted for this follow-up, instead data will be collected from sources such as patient medical records, BronchUK^19^ and/or EMBARC^20^ registries or routinely collected Hospital Episode Statistics (HES) and Office of National Statistics (ONS) data.

At the end of their trial participation, participants will stop taking trial medication and continue to have their condition managed through the standard care pathway.

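### Table 1 sets radiologically confirmed pneumonia as an outcome, but the only measure it states is asking participants, which cannot establish that confirmation

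*Protocol article*

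**What the plan says.** The point sits in one row of Table 1 (protocol article, Objectives and outcomes).

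- **Objective:** "Rates of radiologically confirmed pneumonia, compared with participant’s normal baseline".
- **Measure and method:** "Number of pneumonia events and total number of participants suffering pneumonia. This will be measured by asking the participants during follow-up visits". The requirement for radiological confirmation is no longer there, and the row names no other source.

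Other event rows of the same table do name records. Admissions for bronchiectasis exacerbation are to be "verified where possible by hospital discharge summary/Hospital Episode Statistics (HES) data". All-cause emergency admissions fall back on primary care records where needed, and mortality comes from medical or national statistics records.

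Table 3 (Follow-up visits and participant assessments) places visits at 1, 6 and 12 months. It lists adverse event reporting at the visits and at the telephone calls, and "Review of primary care records" at 12 months. It has no follow-up item for pneumonia or chest imaging. The Pharmacovigilance section has adverse events recorded in the medical notes and the case report form. It exempts events that the investigator judges to be the usual pattern of bronchiectasis.

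The Introduction says that, in COPD, "ICS reduce COPD exacerbation rates but increases pneumonia rates, a side effect that may be very pertinent in bronchiectasis".

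**The concern.** The outcome as named and the method as stated do not fit together. A participant can say that a doctor mentioned pneumonia or that an X-ray was taken. Without a check against a source, neither statement shows that imaging confirmed pneumonia, nor that anything changed from the participant's baseline.

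Confusion is plausible in this population. The protocol's exacerbation is a worsening of cough, sputum, breathlessness or fatigue that needs antibiotics, and a lay person might describe pneumonia in the same terms. Entry requires at least two exacerbations within a 12-month period, so occasions for confusion should be common. The gaps between visits are 5 and 6 months. The weekly diary is described as recording exacerbations and what was done about them, not pneumonia.

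The triple-versus-dual safety comparison is at stake. By Table 2 those two inhalers differ only in the corticosteroid, and pneumonia is the corticosteroid side effect that the Introduction mentions. False reports that are similar in both arms dilute a true difference, so a reassuring ratio near 1 would be hard to interpret.

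**Working it through.** **1. Can another passage supply the confirmation?**

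| Route | Where | Linked to the pneumonia outcome? |
|---|---|---|
| Asking participants at visits | Table 1 | Yes, the only stated method |
| Adverse event reporting at visits and calls; expedited reporting of serious events | Table 3; Pharmacovigilance | No |
| Primary care record review at 12 months | Table 3 | No |
| Discharge summaries and HES | Table 1, bronchiectasis admissions row | No |
| Imaging reports during follow-up | Not mentioned | No |

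Routes that could support a check exist, but the article connects none of them to this outcome.

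**2. Direction and size of the effect.** The article states no pneumonia risk, sensitivity, specificity or power, so there is no figure to reproduce. Every risk and accuracy value below is an assumption. Only the arm size comes from the document (Sample size calculations): 240 per active arm less 5% loss, 240 × 0.95 = 228.

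With the same sensitivity (Se) and specificity (Sp) in both arms, a true 12-month risk p is observed as

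p_obs = p × Se + (1 − p) × (1 − Sp).

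Take 3% (dual) and 6% (triple), true ratio 2.0, Se = 0.70.

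- Sp = 0.99
  - dual: 0.03 × 0.70 + 0.97 × 0.01 = 0.0307
  - triple: 0.06 × 0.70 + 0.94 × 0.01 = 0.0514
  - ratio: 0.0514 / 0.0307 = 1.67
- Sp = 0.97
  - dual: 0.0210 + 0.97 × 0.03 = 0.0501
  - triple: 0.0420 + 0.94 × 0.03 = 0.0702
  - ratio: 0.0702 / 0.0501 = 1.40

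With no false positives the ratio would stay at 0.042 / 0.021 = 2.0. False reports therefore cause the attenuation of the ratio; missed events alone do not.

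**3. Range over other assumptions.** FP = 1 − Sp. Power is for a two-sided 5% comparison of two proportions with n = 228 per arm:

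Φ{[|p1 − p0|√n − 1.96√(2p̄(1 − p̄))] / √(p0(1 − p0) + p1(1 − p1))},

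where p0 and p1 are the observed risks and p̄ is their mean. Each cell gives observed ratio, then power.

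| True risk, dual v triple | Perfect | Se 0.80, FP 2% | Se 0.70, FP 5% | Se 0.60, FP 10% |
|---|---|---|---|---|
| 3% v 4.5% | 1.50, 13% | 1.27, 8% | 1.14, 6% | 1.07, 4% |
| 3% v 6% | 2.00, 34% | 1.54, 19% | 1.28, 12% | 1.13, 7% |
| 5% v 10% | 2.00, 53% | 1.66, 34% | 1.39, 21% | 1.20, 12% |
| 8% v 12% | 1.50, 30% | 1.38, 20% | 1.25, 14% | 1.14, 9% |

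The ratio moves towards 1 in every row. Even perfect ascertainment gives no more than 53% power in these examples.

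**The case against.** The strongest reply is that pneumonia does not depend on recall alone. Inhalers are shipped about monthly, each shipment is followed by a call at which adverse events are taken, serious events are reported within 24 hours of awareness, and primary care records are read at 12 months. Pneumonia is not among the listed examples of exempt bronchiectasis symptoms, although the investigator decides what is exempt. The article also condenses a full protocol, and separate data management and validation plans exist. Asking the participant could simply be what prompts a site check.

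Part of this stands. A reader might infer that the trial has no means of verifying pneumonia, and the documents do not support that. What remains is that none of these routes is linked to the outcome. The mismatch is not just omitted detail either: the row fixes a method, and that method does not deliver what the objective names.

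Three other strong readings should be resisted.

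- A reader might infer that pneumonia was the reason for the trial. The Introduction says only that it may be pertinent, and rests the need for study on the likely bacterial and inflammatory load.
- A reader might take the objective's baseline to be baseline imaging. The text does not say so, and it could mean the participant's usual frequency of pneumonia.
- A reader might conclude that the plan will hide a corticosteroid harm. The accuracy of self-report here is unknown, and few events would limit this comparison under any ascertainment.

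**Conclusion.** The point holds as an inconsistency between a secondary objective and its stated measure. Followed literally, Table 1 would report self-declared pneumonia as radiologically confirmed pneumonia.

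The likely consequence is attenuation of the triple-versus-dual ratio. That direction is an inference: it assumes that blinding makes reporting errors similar across arms. If false reports follow exacerbations and exacerbation rates differ by arm, the errors need not be fully balanced. The size cannot be derived from the document, and the figures of 1.67 and 1.40 in place of 2.0 are illustrations only.

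The primary exacerbation analysis is unaffected. The correction is worth making because the comparison concerns a side effect that the article itself raises, and because a check can use existing records.

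**What to change.** Reword the measure in Table 1 along these lines.

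1. A participant report, an adverse event or serious adverse event report, or a record entry triggers a check of existing records by someone blind to allocation.
2. An event counts as radiologically confirmed only if an existing chest imaging report supports it, or a discharge summary or clinical record that cites one.
3. HES and GP entries serve as triggers and not as confirmation on their own, since nothing in the document shows that they hold imaging findings.
4. Include pneumonia in the 12-month primary care record review, so that events participants do not mention can be found.
5. Tabulate unconfirmed reports separately, by arm.
6. State what the objective's normal baseline means and where it is recorded.

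No new imaging or visits are needed. The cost is a modest record look-up by site staff. Recruitment closed in October 2022 and last visits were due in October 2023 (Trial status), so part of this look-up would be retrospective. The main downside is that pneumonia that was never imaged drops out of the confirmed outcome. The objective as worded already implies that, and the separate table keeps such events visible.
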